##### Additional Project Specific Variables

In addition to these annual, general measures, we will use measures dependent on the specific topic of the local prevention project. Depending on the outcomes in phase 1, the projects could focus on lifestyle or social connectedness and measures added could include variables such as loneliness, mental well-being and physical condition. The methods to evaluate these variables will be determined together with the co-researcher of the team and may consist of validated questionnaires measuring a certain variable (e.g., Lubben Social Network Scale), interviews, focus groups or other qualitative methods of obtaining data, for example through photo voice, elicitation or narrative techniques.

#### 2.4.2. District Nurses

##### Job Satisfaction and Motivation

The impact on job satisfaction of the DN will be evaluated using a selection of 17 out of 77 questions from the standard annual Buurtzorg job satisfaction questionnaire (see Supplementary Materials, Questionnaire S2). This selection contains the questions that are most relevant to job satisfaction in relation to this project. The DN of the participating Buurtzorg teams who have a key role in the development of the prevention project will complete this questionnaire once every year. We will also obtain mean scores on these 17 items of Buurtzorg employees who do not participate in the study. This will provide us with a control measure, so we can compare the change over the course of this study between the involved nurses in our programme and those involved in regular care of Buurtzorg. Similarly, we will collect data that Buurtzorg has on mean hours of care per client to track the changes during our project and compare the participating teams with regular teams.

The researchers will conduct individual semi-structured interviews in the first and last year of the project to gather information about DN’s views on preventive care, their motivations to work on prevention, the relation to community care and their view on the prevention project in their team. We will ask questions such as “How does prevention fit into the work of DN according to you?”, “How was the subject of prevention represented in your education and how does this relate to your current view on prevention?”, “Can you name some positive and some less positive aspects of your team’s collective prevention project?” (see Supplementary Materials, Topic list S2). These interviews will be followed by focus groups with each Buurtzorg team with a topic list that transpires from the outcomes of the individual interviews. Topics that are likely to be discussed are different views on prevention, representation of prevention in education, roles in and views on the Collective Prevention programme and collaboration within the team. Prior to these interviews, we obtained informed consent from the DN.

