### 2.2. Design

As previous results of population wide prevention have been difficult to establish and this project takes place in the community, we choose an iterative, practice-based design that allows us to make ongoing adjustments during the implementation process. A participatory action research design fits the need for both responsiveness and a contextual approach. We will use mixed methods of data collection to gather insights in implementing public prevention in our healthcare system together with community members and Buurtzorg DN. The aim is that these insights allow all Buurtzorg teams to organise prevention programmes in their localities. Therefore, we will study the motivations of DN to work on prevention and the required qualities and knowledge of DN to successfully establish a prevention programme. The participatory action research approach allows us to immediately respond to the insights we gather during the project, so we can continue to evaluate and adapt the process during the project. For immersive collaboration with DN, every participating Buurtzorg team will choose one team member to be the co-researcher in this project, who will be in regular contact with the action researcher RK. As participatory action research is about doing research *with* instead of *on* people, these co-researchers will have a broad role in the entire project. They will be involved in data collection, reflections on the process of the study and their own experiences, contributing to the projects of other teams by sharing the lessons they learn along the way and helping to interpret the analysed data.

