### 2.6. Analyses

#### 2.6.1. Quantitative Analyses

For the quantitative analysis we measure three dependent variables (quality of life, experienced health and social participation) in all of the 14 prevention programmes once a year. We estimate that 25–30 community members will be involved per locality, resulting in a sample size of 350–420 individuals. All variables will be analysed descriptively per year. We will use a repeated measures MANOVA to assess the change within subjects for the dependent variables over time (4 time points). We will use the same test to make between-group comparisons of the individual prevention programmes if the sample size allows this.

Quantitative project specific measures will most likely have an inadequate sample size for a solid quantitative analysis, so these will only be analysed descriptively. In case of multiple teams using the same project specific measure (e.g., Lubben Social Network Scale), we may be able to make comparisons in change of these variables over time and between the different projects. As Buurtzorg teams will determine the design of their project depending on the findings in phase 1, we cannot determine this in advance.

Job satisfaction will be analysed descriptively every year. The change over the years (4 measurement times) will be compared within subjects using a repeated measures ANOVA. We will also conduct a t-test to compare the change in job satisfaction for participating DN with the larger group of Buurtzorg DN who do not participate in the study but answer the same questions as part of the standard annual Buurtzorg questionnaire. The same analysis will be performed on the mean hours of care per client per Buurtzorg team, except in this case each data point represents a team instead of an individual.

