The development and implementation process can be time consuming for DN and will include tasks that normally lie outside the scope of their daily work. Therefore, we expect to encounter unforeseen difficulties and challenges along the way. It may also lead to fluctuations in work satisfaction during the project. The population of DN in this study is highly motivated to work on prevention, so we expect that their work satisfaction will eventually increase once the prevention projects are well underway. The effect of motivation patterns on success will also be studied, which can be used as a guideline or criterion for starting a prevention project in a certain team of DN.

We also aim to shed light on other working elements such as required skills, knowledge and appropriate steps to take when organising a collective prevention project. As we expect community engagement to be an important factor in each projects’ success, we will compare our results with the conceptual model for community engagement and pay special attention to elements such as organizational partnerships and alliances [51]. While these partnerships are not specifically assessed in this project, we acknowledge their importance and would suggest more detailed investigation on this topic for future steps of this project. We aim to create a general timeline and guidelines to make implementation of collective prevention programmes possible on a broader scale.

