## Figures and Tables

**Figure 1 ijerph-20-03134-f001:**
[figure not shown]
Impact measurements of collective prevention projects. Note: Q = questionnaire, I = Interview, F = focus group. CR = Co-researchers: the district nurses who have an active role in the development of the prevention projects.

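### Job-satisfaction respondents are defined by project role, with no statement of when the role is fixed or whether nurses who lose it are still surveyed; the comparator appears to be yearly means of an open group

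*Protocol article*

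**What the plan says.** Section 2.4.2 (Job Satisfaction and Motivation) takes 17 of the 77 items in the employer's standard annual questionnaire. The respondents are nurses of participating teams "who have a key role in the development of the prevention project will complete this questionnaire once every year". For comparison, the study will obtain mean scores on the same items for employees outside the study.

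Section 2.6.1 plans two analyses. The first is within the participating nurses: "The change over the years (4 measurement times) will be compared within subjects using a repeated measures ANOVA". The second is a comparison: "We will also conduct a t-test to compare the change in job satisfaction for participating DN with the larger group of Buurtzorg DN", the latter being those outside the study.

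The role is worded in several ways. Section 2.2 says that "every participating Buurtzorg team will choose one team member to be the co-researcher in this project". The note to Figure 1 describes co-researchers as "the district nurses who have an active role in the development of the prevention projects". Section 2.4.2 speaks of a key role and of involved nurses, and section 2.6.1 of participating nurses.

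Section 3.1 expects the work to be time consuming and partly outside the nurses' usual tasks. It says of this: "It may also lead to fluctuations in work satisfaction during the project". It then expects satisfaction to rise once the projects are well underway.

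**The concern.** A project role can change hands during the 4–5 years for which section 2.2 follows the teams. The respondents are defined by that role, not by team membership or a list drawn up at the start. If the rule is applied afresh each year, a nurse who hands over the role stops contributing scores and her successor enters without a baseline. The change that is analysed then describes nurses who stayed in the role.

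Section 3.1 makes it plausible that nurses for whom the project goes badly are the ones who step back. Selective exit of this kind would produce the same picture that section 3.1 predicts from a real benefit: early fluctuation, then a rise. The limitations (section 3.2) acknowledge that teams are selected for motivation at entry, but not that nurses may be selected by exit.

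The comparison has a separate weakness. Mean scores of employees outside the study appear to describe whoever is employed and answers in a given year, including new hires and excluding leavers. The difference between two such means is not within-person change, yet it is to be compared with change in the participating nurses.

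**Working it through.** The article gives no sample size, SD, expected effect or dropout for job satisfaction, so there is no stated figure to reproduce. The check is a reading of the text, followed by an illustration.

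**1. When is the role fixed?** Section 2.4.2 gives no time point. Section 2.3 puts baseline at the start of the project, whereas section 2.2 has the prevention project designed only in the third phase, with delays that differ between teams. A key role in developing a project may therefore not be fully known at baseline. Section 2.6.1, by planning a within-subject analysis, suggests that the same nurses are followed. The text allows both a cohort fixed once and a role judged yearly.

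**2. What follows if the role is judged yearly?** A conventional repeated measures ANOVA over four time points uses only nurses with all four scores, here those who kept the role throughout. The t-test is not stated to need all four scores. It still needs a later score, and a nurse no longer surveyed has none.

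**3. How many nurses are meant?** One co-researcher per team gives 18 nurses. All members of 18 teams of 6–12 nurses (section 2.1) gives 18 × 6 = 108 to 18 × 12 = 216. The number with a key role is not given.

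**4. Illustration of the possible bias.** Let p be the share of starters who have left the role by the fourth measurement, S the mean change in stayers and L the mean change in leavers.
- Mean change in all starters = (1 − p)S + pL.
- Overstatement when only stayers are used = S − [(1 − p)S + pL] = p(S − L).
- With a constant yearly exit rate a over three intervals, p = 1 − (1 − a)³.

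Both a and S − L are assumptions; neither is in the article.

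| Yearly exit a | Stayers (1 − a)³ | p | S − L = 0.2 SD | 0.5 SD | 0.8 SD |
|---|---|---|---|---|---|
| 5% | 0.857 | 0.143 | 0.03 | 0.07 | 0.11 |
| 10% | 0.729 | 0.271 | 0.05 | 0.14 | 0.22 |
| 15% | 0.614 | 0.386 | 0.08 | 0.19 | 0.31 |
| 20% | 0.512 | 0.488 | 0.10 | 0.24 | 0.39 |

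If leaving is unrelated to change in satisfaction, S − L = 0 and the overstatement is zero.

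**5. Could former role-holders distort the comparison mean?** Hardly. The 18 participating teams are 18/950 = 1.9% of all the employer's teams (950 in section 3.1). Any bias from exit would lie mainly on the participating side.

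**The case against.** The strongest reply is that the article never says the role must be current. The sentence can equally be read as naming a group once and surveying it yearly, and the within-subject analysis fits that reading. This stands. A reader might infer that nurses who give up the role leave follow-up by rule, but the article states no such rule.

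A reader might also infer that such a nurse automatically moves into the comparison group. The text does not support this: the comparator is "the larger group of Buurtzorg DN who do not participate in the study", not nurses without a key role, and study participation also includes interviews and team focus groups.

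Nor is the Figure 1 note shown to contradict section 2.2. Its plural fits 18 teams with one co-researcher each, and the figure itself is not available here. What remains is that the article never says how key role relates to co-researcher.

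A condensed article may leave the handling of leavers and missing scores to a fuller document, and silence on that alone would be no finding. The point rests on what is stated: a role-based rule for who responds, a within-subject analysis, and a comparator described only as means.

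Finally, job satisfaction is not among the objectives listed in section 3, although the Introduction names nurses' work satisfaction among the effects to be evaluated. This limits the weight of the point but does not remove it.

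**Conclusion.** The concern holds in a conditional form. Respondents are defined by a role whose timing is not fixed, and nothing in the article keeps former role-holders in follow-up. If the role is applied at each survey, the reported change is that of nurses who kept it, with a bias towards apparent improvement if dissatisfied nurses step back. The mismatch between within-person change and what appear to be yearly means of an open group holds under either reading.

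The size is unknown. The 0.14–0.24 SD at 10–20% yearly exit rests wholly on the assumed exit rates and the assumed 0.5 SD difference, and should not be quoted as an estimate. It also treats all leavers alike, whereas only those still employed could be recovered by a better rule. This is an inexpensive improvement to a stated rule. It is not evidence that the job-satisfaction result will be wrong.

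**What to change.** Amend sections 2.4.2 and 2.6.1 as follows.

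- List the participating nurses at their team's baseline, and state whether key role means the co-researcher only or all involved nurses.
- Have every listed nurse complete the 17 items each year while employed, whatever her later role or the status of her team's project. Use the study questionnaire, or her answers to the employer's survey if these are linkable and she consents. The article does not say that they are linkable.
- Replace the repeated measures ANOVA with a model that keeps incomplete series, such as a linear mixed model.
- Keep the listed nurses and the 18 teams out of the comparison means in all years.
- Use one membership rule on both sides: either nurses employed at baseline, or yearly cross-sections for both.
- Report how many leave the role, the team and the employer.

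The cost is a baseline list, consent, and some questionnaires to nurses no longer in the role. The items already belong to the annual survey, so no new instrument is needed. The list and consent have to be in place at baseline. Nurses who leave the employer may remain unmeasured, so some selection would persist.

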### 2.3. Procedure

In the learning process of participative action research, qualitative methods can provide context specific and detailed information from the different perspectives of participants. Therefore, we keep the number of questionnaires to a minimum. Furthermore, long questionnaires can discourage community members from participating in the study, due to the time investment and possibly a perceived breach of their privacy. The general attitude of DN towards questionnaires is not positive either. They indicated that they prefer personal and informal communication with community members to build and maintain a relation of trust. After discussion, we have selected three questionnaires amounting to 18 questions in total and a selection of 17 questions from an annual employee questionnaire from Buurtzorg. We will start with a baseline measurement at the start of the project and repeat the data collection annually for four years, resulting in a total of four measurement times during the project.

During these four years, the researcher will conduct a number of interviews and focus group discussions to evaluate the process and gain insights in the experiences the DN and the community members during the project. These meetings will be voice- and/or video-recorded after permission from the participants. Observations about the atmosphere, non-vocal communication and other contextual information will be noted. In addition to the standard evaluation and measurements for every prevention project, we may deploy other methods for project specific outcomes in collaboration with the co-researchers. This will ensure that the methods suit the specific projects and their envisioned targets and that co-researchers are satisfied with the way their projects are evaluated.

Throughout the whole project, Buurtzorg teams will receive support from one of the three Buurtzorg coaches who are part of the project team for the organisation of the Collective Prevention programme. Additionally, the researcher will have monthly contact with the co-researchers to gather experiences from the team and evaluate the process of developing a collective prevention project. Finally, (participatory) observations will be made throughout the duration of the study, for example during brainstorm sessions, meetings or activities of the prevention projects.

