### 3.2. Limitations

This study will take place in 14 different localities with prevention projects that are designed for that specific context. This makes the projects relevant for the neighbourhood, but also comes with challenges in generalisability and comparing the prevention projects and their health and social effects. For example, the effects could be different for different ethnic groups due to underlying differences in views and perceptions regarding health, social norms and collective prevention. This should be taken into account if prevention projects are deployed in more localities. Additionally, the participating Buurtzorg teams are not selected at random, but they apply for participation in the project and are selected based on a strong motivation and willingness to work on prevention. This means that the sample of district nurses in this project likely already has a certain set of characteristics or values that are different from a randomized sample. It should, therefore, be noted that the implementation of collective prevention programmes in all Buurtzorg teams may shine light on new challenges or required skills and knowledge that may have been taken for granted in the selected sample of the current study. Furthermore, it is difficult to accurately measure prevention, as the desired outcome is a non-event. In addition, there is no control group in this study and we can only compare with general population outcomes. Furthermore, we are not able to control for the effect of planning and organizing a project in a community. Structural Governance and Collective Empowerment are two practices in community-based participatory research that influence the outcomes through interaction with the context, relationships and other aspects of the research [52]. This means that the health and social effects that we will measure cannot only be attributed to the content of the prevention project. Finally, results in this study will mainly be based on a population of relatively older people, since they are more likely to have the time to help organise such a project. Whereas collective prevention should be focused on all ages, as this is the best way to collectively change our lifestyle and prevent age-related diseases. This may be a next step for spreading the prevention projects of this study.

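### Hours of care and job satisfaction are compared from project start onward only, so an earlier difference in trend between self-selected and regular teams could be neither seen nor separated from a project effect

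*Protocol article*

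**What the plan says.** Section 2.3 fixes when measurement begins: "We will start with a baseline measurement at the start of the project and repeat the data collection annually for four years". It counts four measurement times in all.

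Section 2.4.2 (Job Satisfaction and Motivation) names two outcomes with a Buurtzorg comparator:
- **Job satisfaction** uses "a selection of 17 out of 77 questions from the standard annual Buurtzorg job satisfaction questionnaire". Participating nurses with a key role in the project answer it. For non-participating employees, mean scores are obtained "so we can compare the change over the course of this study between the involved nurses in our programme and those involved in regular care".
- **Hours of care per client** come from records that the organisation already holds: "Similarly, we will collect data that Buurtzorg has on mean hours of care per client to track the changes during our project". Participating teams are compared with regular teams.

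Section 2.6.1 gives the analysis. For job satisfaction: "The change over the years (4 measurement times) will be compared within subjects using a repeated measures ANOVA". A t-test then compares the change with that of non-participating nurses. Hours of care are analysed in the same way, with the team as the unit.

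Section 3.2 says that the teams "are selected based on a strong motivation and willingness to work on prevention". It treats this as a caution about extending the programme to all teams, not as a possible bias in these two comparisons.

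**The concern.** A comparison of change removes two things: a fixed difference in level between the groups, and any movement shared by all teams. It does not remove a difference in trend that was there before the project. The comparison can be read as a project effect only if participating and regular teams would otherwise have moved in parallel. Data that begin at project start cannot test this.

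Parallel movement is open to doubt here because teams volunteered and were then selected on motivation and capability. Section 3.1 itself links that motivation to the expected course of work satisfaction.

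These are the only analyses in the article with a concurrent comparator, and section 2.4.2 calls the comparator a control measure. Section 3.1 expects less nurse workload and aims to extend the programme to all 950 teams. A misleading signal on hours of care would feed directly into that argument. Both outcomes come from standing sources, so earlier years may be available at little cost.

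**Working it through.** The article gives no SD, correlation, trend or power for these outcomes, so there is no planned figure to reproduce. What follows shows how an assumed prior trend passes through the planned test.

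**Inputs**
- Participating teams: 18 (section 2.1).
- Comparator teams: 950 − 18 = 932 (950 from section 3.1; using all the others is an assumption).
- Interval: first to fourth measurement, three years (assumption; section 2.6.1 does not say which interval the t-test uses).
- Year-to-year correlation 0.7, one-year SD set to 1, true effect zero, two-sided 5% test (assumptions).

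**Planned t-test on change**
- Variance of one team's change: 2 × (1 − 0.7) = 0.60.
- 1/18 + 1/932 = 0.0566.
- SE of the difference: √(0.60 × 0.0566) = 0.184 SD.

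| Prior trend difference (SD per year) | False effect over 3 years (SD) | Rejection |
|---|---|---|
| 0.05 | 0.15 | 13% |
| 0.10 | 0.30 | 37% |
| 0.15 | 0.45 | 68% |

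**Sensitivity to scale.** If the trend is expressed in SDs of the change score, 0.05, 0.10 and 0.20 per year give 9.7%, 24.2% and 71.2% rejection. The pattern is the same and the percentages move with the scale chosen.

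**What earlier years can do.** A simulation used 2,000 runs per setting, three pre-project years, linear trends, between-team SD 1, yearly residual SD 0.5 and no true effect. With prior trend differences of 0, 0.05, 0.10 and 0.20 between-team SD per year:
- the planned test rejected in 4.6%, 15.2%, 44.0% and 93.5% of runs;
- after subtracting each team's extrapolated pre-project slope, rejection was 4.7%, 4.9%, 4.5% and 5.3%, with bias about zero.

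**What it costs in precision.** Take correlation 0.7 (residual variance 0.30 per year), three pre-project years and three project years:
- Departure of the project-year mean from each team's own extrapolated trend: 0.30 × (1/3 + 1/3 + 9/2) = 1.55, so SE = √(1.55 × 0.0566) = 0.296 SD.
- Step model with one common slope: 0.30 / (1.5 − 4.5²/17.5) = 0.30 / 0.343 = 0.875, so SE = √(0.875 × 0.0566) = 0.223 SD.
- Both exceed the planned test (0.60, SE 0.184 SD).

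**How well three earlier years show a trend difference.** The variance of one team's slope is 0.30/2 = 0.15, so the SE of the slope difference is √(0.15 × 0.0566) = 0.092 SD per year and the 95% interval is about ± 1.96 × 0.092 = ± 0.18. Three years would expose a large difference but could not rule out one of 0.05 to 0.15.

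**The case against.** Several points on the other side have force.

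- **The article does not forbid earlier data.** A reader might infer that it does. The wording on hours of care states a purpose, not an extraction window, and a look-back period could sit in a fuller document. That stands as a limit on the reading. What the article does fix is a baseline at project start, four measurement times and a test on change over the study, and no pre-project year enters any of these.
- **No prior trend is documented.** A reader might infer that the study will report a false effect. The article supports only the conditional statement: if a trend difference exists, it goes into the result unseen. Every size shown rests on assumption.
- **Rebound from an untypical selection year.** This is tempting but speculative. Teams were selected on motivation and capability, not on satisfaction scores or hours.
- **Earlier data as a gain in precision.** A reader might infer this from a level-adjusted analysis of three pre-project and three project years: its variance is 0.80 − 0.49/0.80 = 0.19 against 0.60, about 31%. That analysis does not remove a trend. Most of its gain also needs no earlier data: one baseline with three project years gives 0.80 − 0.49 = 0.31, which is 0.29 of the 0.41 reduction. Removing the trend loses precision.
- **Job satisfaction is harder.** The comparator is mean scores only, the respondents are key-role nurses, and the planned unit is the individual, so the 18 against 932 calculation does not describe that test. That the survey is annual suggests earlier answers exist, but whether they can be retrieved or linked is not stated. This stands, and makes the remedy conditional for this outcome.
- **Weight.** Neither outcome belongs to the first primary objective, and section 3.2 discloses the non-random selection and the absence of a control group. That lowers the priority. It does not answer the point about prior trends.

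**Conclusion.** The point holds in conditional form. As written, the comparisons of hours of care and job satisfaction cannot detect a difference in trend that preceded the project, nor separate it from a project effect. If one exists, it enters the t-test in full: 0.15 to 0.45 SD over three years, with 13% to 68% rejection, for an assumed prior difference of 0.05 to 0.15 SD per year. This rests on 18 against 932 teams, correlation 0.7, a three-year change and no true effect.

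The case is firm for team-level hours of care, where the organisation is said to hold the data. It is conditional for job satisfaction. The plan should be changed on this point, but it concerns supporting outcomes and does not affect the community health measures.

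**What to change.** In sections 2.4.2 and 2.6.1:

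1. Request the hours-of-care figures for about three years before the teams applied, for participating and regular teams.
2. Compare the pre-project slopes of the two groups first. Report the difference with its confidence interval, not as a pass-or-fail test, because three years leave an interval of about ± 0.18 SD per year under the assumptions above.
3. In the main comparison, use the pre-project mean as baseline adjustment. This replaces reliance on one baseline year but leaves any trend difference in place.
4. Add a sensitivity analysis that removes the pre-project trend.
5. If the earlier slopes clearly differ, report the between-group difference as descriptive only.
6. Do the same for the 17 satisfaction items only where earlier team-level means can be retrieved for both groups, and state that team means cover a different group from the key-role nurses.

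The cost is one extended data request and a longer analysis, with no new measurement and no added burden on nurses. The drawback is precision: the trend-removed estimate has an SE of about 0.22 to 0.30 SD against 0.18 SD for the planned t-test. That is why it is proposed as a sensitivity analysis.
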